## **6.7 Premature termination of the study**

Parents/legal guardians and children have to fill out several questionnaires. Children participate in the study for a period of 10 weeks. It is expected that these measurements and interventions do not involve any risks for the participants. Therefore no criteria are formulated for premature termination of the study.

## **7. SAFETY REPORTING**

Timely, accurate, and complete reporting and analysis of safety information from clinical studies are crucial for the protection of subjects, investigators, and the sponsor, and are mandated by regulatory agencies worldwide. The sponsor has established Standard Operating Procedures in conformity with regulatory requirements worldwide to ensure appropriate reporting of safety information; all clinical studies conducted by the sponsor or its affiliates will be conducted in accordance with those procedures.

All adverse events will be reported from the time a signed and dated informed consent form is obtained until completion of the subject's last study-related procedure. An adverse event is any untoward medical occurrence in a clinical study subject administered a procedure. An adverse event does not necessarily have a causal relationship with the treatment. An adverse event can therefore be any unfavorable and unintended sign (including an abnormal finding), symptom or disease temporally associated with the use of a procedure, whether or not related to that procedure. However, for this study we will only collect adverse events that are possibly, probably or very likely related to the study procedures.

The Sponsor will evaluate any safety information that is spontaneously reported by an Investigator beyond the time frame specified in the protocol.

## 8. STATISTICAL ANALYSES

The modified ITT analysis set will include all randomized subjects who have both a baseline and at least one post-baseline efficacy assessment. Hochberg procedure (Biometrika, 1988) will be used to control the experiment-wise alpha level at 0.05 for the multiple primary endpoint analyses. All tests will be two-sided.

For all outcome measures descriptive statistics (mean, SD, median and range) as well as their changes from T0 (Baseline) will be calculated by treatment group. Within-group comparisons of changes at T1 (Week 10) from T0 will be conducted in both groups.

To assess whether effects are maintained after stopping the game, within-group comparisons of changes at T2 (Week 20) versus T1 will be performed in the Immediate group. To assess effects of game after waiting period, within-group comparison of changes at T2 versus T1 will be conducted in the delayed group.

An analysis of covariance (ANCOVA) model that includes treatment, site and gender as factors and baseline as covariate, will be used for the primary outcome measures to estimate the difference between the two groups in changes from T0 at T1.

Exploratory analyses may be conducted as deemed appropriate to examine whether intervention effects vary as function of demographic and baseline characteristics (e.g. age, gaming experience), to explore correlations between different measures, to investigate potential mediating effects (e.g. working memory, self-efficacy).

All adverse events will be listed. Special attention will be given to those subjects who discontinued due to an adverse event.

## **9. ETHICAL CONSIDERATIONS**

### **9.1 Regulation statement**

The current study does not concern a medical intervention but a study to on the effectiveness of the HealSeeker as a cognitive and behavioural intervention. The goal of this training is to enhance time management, organisational skills, planning and social skills in children with ADHD through a computer game with built-in learning strategies. Some principles of the declaration of Helsinki (Seoul, 2008) are applicable to this study. According to this declaration, the primary goal of medical research involving humans is improving preventive, diagnostic and therapeutic procedures and understanding the aetiology and pathogenesis of an illness/disorder. The parents/legal guardians and children will be correctly informed about the goals, methods and possible discomforts of the training. Also, all participants and their parents/legal guardians will be informed on their right of denying participation or withdrawal at any moment in the study, without any further consequences (World Medical Association Declaration of Seoul, 2008). The study will be conducted according to the principles of the Declaration of Helsinki (Seoul, 2008) and in accordance with the Medical Research Involving Human Subjects Act (WMO) for the Netherlands and Wet Inzake Experimenten op de Menselijke Persoon for Belgium and other guidelines, regulations and Acts.

### **9.2 Recruitment and consent**

Participants will be children with ADHD 8 to 12 years old, recruited through the research site in the Netherlands and Belgium. The investigator will approach the parents/legal guardians and the children and shortly inform them about the research. When parents/legal guardians and the children are interested in participating in the study, they are invited for a screening visit/ T0 visit (prior to randomization), where the study is further explained. If parents/children want they can also receive an envelope containing the informed consent for the parents/legal guardians, an informational pamphlet (informed assent) for the child and a written informed consent at home. The information is about how study to the learning effects of a Serious Game will be conducted. In addition, parents/legal guardians and their child will be invited to participate in the study. Both parents/legal guardians and twelve-year-olds will be asked to sign the written informed consent. The informed consent/ assent clearly states that participants are allowed to withdraw at any moment in the study without further consequences or reason. The practitioner will emphasise that choosing to join or not will not affect in any way the treatment the child is currently receiving at the mental health care institution. In accordance with the Dutch WMO and Belgium law (Wet Inzake Experimenten op de Menselijke Persoon), parents/legal guardians will have to sign a written informed consent. Parental consent is crucial for joining the study. Parents/legal guardians have to

give their consent for the approach of the teacher by the researchers. If the participant is twelve years of age he or she will have to sign an informed consent, in addition to their parent. The informed consent obtained from the parent or his or her legally acceptable representative includes explicit consent for the processing of personal data and for the investigator/institution to allow direct access to his or her original medical records (source data/documents) for study-related monitoring, audit, IEC/IRB review, and regulatory inspection. This consent also addresses the transfer of the data to other entities and to other countries. The researcher will sign all informed consents. After receiving the signed informed consent, parents/legal guardians will be contacted by phone to decide if an IQ test is needed, and appointments will be made for the measurement moments.

### 9.3 Investigator Responsibilities

The investigator is responsible for ensuring that the study is performed in accordance with the protocol, current ICH guidelines on Good Clinical Practice (GCP), and applicable regulatory and country-specific requirements. Good Clinical Practice is an international ethical and scientific quality standard for designing, conducting, recording, and reporting studies that involve the participation of human subjects. Compliance with this standard provides public assurance that the rights, safety, and well-being of study subjects are protected, consistent with the principles that originated in the Declaration of Helsinki, and that the study data are credible.

### 9.4 Independent Ethics Committee or Institutional Review Board

Before the start of the study, the sponsor will provide the IEC/IRB with current and complete copies of the following documents (as required by local regulations):

- Final protocol and, if applicable, amendments
- Sponsor-approved ICF/Assent (and any other written materials to be provided to the subjects)
- Sponsor-approved parent recruiting materials
- Information on compensation for study-related injuries or payment to subjects for participation in the study, if applicable
- Investigator's curriculum vitae or equivalent information (unless not required, as documented by the IEC/IRB)
- Information regarding funding, name of the sponsor, institutional affiliations, other potential conflicts of interest, and incentives for subjects
- Any other documents that the IEC/IRB requests to fulfill its obligation

This study will be undertaken only after the IEC/IRB has given full approval of the final protocol, amendments (if any, excluding the ones that are purely administrative, with no

consequences for subjects, data or study conduct), the ICF, applicable recruiting materials, and parent compensation programs, and the sponsor has received a copy of this approval. This approval letter must be dated and must clearly identify the IEC/IRB and the documents being approved. During the study the investigator (or sponsor where required) will send the following documents and updates to the IEC/IRB for their review and approval, where appropriate:

- Protocol amendments (excluding the ones that are purely administrative, with no consequences for subjects, data or study conduct)
- Revision(s) to ICF and any other written materials to be provided to subjects
- If applicable, new or revised parent recruiting materials approved by the sponsor
- Revisions to compensation for study-related injuries or payment to subjects for participation in the study, if applicable
- Summaries of the status of the study at intervals stipulated in guidelines of the IEC/IRB (at least annually)
- Any other requirements of the IEC/IRB

For all protocol amendments (excluding the ones that are purely administrative, with no consequences for subjects, data or study conduct), the amendment and applicable ICF revisions must be submitted promptly to the IEC/IRB for review and approval before implementation of the change(s). At least once a year, the IEC/IRB will be asked to review and reapprove this study. The reapproval should be documented in writing (excluding the ones that are purely administrative, with no consequences for subjects, data, or study conduct). At the end of the study, the investigator (or sponsor where required) will notify the IEC/IRB about the study completion.

### **9.5 Objection by minors or incapacitated subjects (if applicable)**

The study is aimed at children of 8 to 12 years of age. Parents/legal guardians have to sign a written consent, but only if their child is willing to participate. If the participant is twelve years of age he or she will have to sign an informed consent (assent), in addition to their parent. Signed informed consent from a parent/legal guardian is crucial for participation. Participants are free to withdraw from the intervention at any time, without further consequences. All participants will have a minimum IQ of 80.

### **9.6 Benefits and risks assessment, group relatedness**

Both children and their parents/legal guardians will be well informed about the goals and used methods in this study, and of the advantages and disadvantages of joining, and brochures for parent and child have been made solely for this purpose. The risks of this

intervention are limited, especially since the study does in no way interfere with regular treatment or education of the children with ADHD. Thereby, the risk of game addiction is negligible. Game addiction occurs in situations of children playing games for more than 40 hours per week (Van Rooij, Schoenmakers, Meerkerk & Van de Mheen, 2009). The maximum game play time per day is set at 45 minutes for both HealSeeker, combined with 20 minutes in the social community (HealSeeker). Because of the limited available game time, the risk of addiction is minimal. In addition, most addictive games have a component of random rewards. This is not the case in HealSeeker in which only positive behaviour is rewarded. Finally, the prevalence rates of game addiction in children 13 till 16 years of age are very low and even lower in younger children. The risk of addiction is not very likely for the age group included in this study. The current study concerns a therapeutic intervention through a computer game. The goal of this training is to enhance time management, organisational skills, planning and social skills in children with ADHD through a computer game with built-in learning goals. The computer game can be played online and at home. The risks of participation can be considered negligible and the burden can be considered minimal. This study provides children with ADHD with the opportunity to join a non-medicinal intervention aimed at abating associated problems and elevating empowerment. Parents/legal guardians and the child can withdraw from the intervention at any moment, without questions or further consequences.

### **9.7 Compensation for injury**

Based on the above mentioned risk taxation, for this study, we wish to obtain dispensation from the statutory obligation to provide insurance, because we presume participating in the study is without risk for which the insurance applies (attachment G1).

## **10. ADMINISTRATIVE ASPECTS AND PUBLICATION**

### **10.1 Handling and storage of data and documents**

All data gathered for this study will be handled anonymously and confidentially. Subjects will receive a code, based on the group they are in (intervention or control) and serial number. Gaming information will be gathered in an online database linked to the personal identification code of the participant. If necessary, data can be traced back to a participant using an identification code list. The main investigator is the only person with access to this list, and safeguards the anonymity of the list. Parents/legal guardians of the participants will be asked permission to keep the information for future research (attachment E2). This treatment of the obtained data conforms to the Law for Protection of Personal Data in the Netherlands and Belgium. In case of publishing, this data will be reported in group form and can in no way be traced back to the individual participants. Electronic Data Capture (eDC) will be used for this study. The electronic file will be considered to be the CRF. Worksheets may be used for the capture of some data to facilitate completion of the CRF. Any such worksheets will become part of the subject's source documentation. All data relating to the study must be recorded in CRFs prepared by the sponsor.

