### **3.2 Design rationale**

In the absence of an appropriate control game a wait list control design was chosen. This design allows to assess the effect of the intervention as add-on to standard care while controlling for potential external confounders. Allocation to treatment group will be done through an automated randomisation process to avoid introduction of bias in treatment allocation. Even though the trial will be open-label, efforts will be made to keep the assessor blinded to the treatment allocation during the trial to avoid bias in the assessment of subject outcome.

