#### *T1 Measurement/T1 visit*

To assess the level of skills one week after the end of the intervention, as well as the satisfaction of the intervention, the following measurements will be done:

Parent/legal guardian:

- Time management (using a self-constructed questionnaire and the It's about time questionnaire)
- Planning (using the planning and organising subscale of the BRIEF)
- Social skills (using a subscale of the SSIS-RS)
- Working memory (using the working memory subscale of the BRIEF)
- Satisfaction regarding HealSeeker (using a self-constructed questionnaire); only applicable for parents/legal guardian of the immediate treatment group

Parents/legal guardians fill out the general questionnaire again at T1 to administer changes regarding current treatment.

Children:

- Planning (using a neuropsychological task; tower test)
- Social skills (using SCVT)
- Working memory (using a neuropsychological task; chessboard task)
- Self-efficacy (using a self-constructed questionnaire)

- Satisfaction regarding HealSeeker (using a self-constructed questionnaire); only applicable for children of the immediate treatment group

Teacher:

- Time management (using a self-constructed questionnaire)
- Planning (using the planning and organising subscale of the BRIEF)
- Social skills (using a subscale of the SSIS-RS)
- Working memory (using the working memory subscale of the BRIEF)

The questionnaire concerning satisfaction of the intervention will be given to children and their parents/legal guardians to assess the degree of satisfaction on HealSeeker. For the immediate treatment group this will be at T1. For the delayed treatment group this will be at T2. The assessor should preferably be blinded for the distribution of this questionnaire. In practice this means someone else of the trial team other than the assessor should take this satisfaction questionnaire, if possible. In this way the assessor will not be influenced by knowing if the child played or did not play the game. The assessor will be asked if he/she has the idea the child played or not, to investigate whether this blinding is broken or not. As the trial is open, it is not mandatory to keep the assessor blinded and information about whether assessor was blinded will be collected.

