## **6.2 Randomisation, blinding and treatment allocation**

Randomisation will be used to minimize bias in the assignment of subjects to treatment groups to increase the likelihood that known and unknown subject characteristics (e.g., demographic and baseline characteristics) are equally balanced across treatment groups (1:1), and to enhance the validity of statistical comparisons across treatment groups.

The randomization list will be stratified by site and gender using randomly permuted blocks.

Randomisation to the immediate and delayed treatment group condition will occur after collection of baseline data and confirmation of eligibility in the web-based ECD system.

The randomization process will be automated and based on a pre-specified computer-generated randomization list. A randomization number will be assigned online using the next available number on the randomization list corresponding with the site and gender of the subject. The trial will be open-label. Due to the nature of the intervention and time frame, it will be obvious for participants, their parents and teachers and the site staff to which treatment group they are allocated. All efforts are made to keep the assessor blind. If a child spontaneously tells the assessor his or her treatment condition, this will be registered.

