### **10.5 Subject Identification, Enrollment, and Screening Logs**

The investigator agrees to complete a subject identification and enrollment log to permit easy identification of each subject during and after the study. This document will be reviewed by

the sponsor study-site contact for completeness. The subject identification and enrolment log will be treated as confidential and will be filed by the investigator in the study file. To ensure subject confidentiality, no copy will be made. All reports and communications relating to the study will identify subjects by subject identification and age. The investigator must also complete a subject screening log, which reports on all subjects who were seen to determine eligibility for inclusion in the study.

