## 10.6 Source Documentation

At a minimum, source documentation must be available for the following to confirm data collected in the CRF: subject identification, eligibility, and study identification; study discussion and date of signed informed consent; dates of visits; results of efficacy parameters as required by the protocol; and date of study completion and reason for early discontinuation of study drug or withdrawal from the study, if applicable. In addition, the author of an entry in the source documents should be identifiable. At a minimum, the type and level of detail of source data available for a subject should be consistent with that commonly recorded at the study site as a basis for standard medical care. Specific details required as source data for the study will be reviewed with the investigator before the study and will be described in the monitoring guidelines (or other equivalent document).

The following data will be recorded directly into the CRF and will be considered source data:

- Questionnaires for parents/ legal guardians;
- Questionnaires for teachers;
- Results on tasks for children (may be added directly in the CRF, but also paper source can be used).

Inclusion and exclusion criteria not requiring documented medical history must be verified at a minimum by subject /parent interview.

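### Section 10.1 builds the subject code from the treatment group, which undercuts the stated, non-mandatory effort to keep the assessor of the child tasks blind

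*Protocol*

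**What the plan says.** On the identifier, protocol section 10.1 states: "Subjects will receive a code, based on the group they are in (intervention or control) and serial number". The same section keeps the list linking codes to named children with the main investigator alone. Section 10.5 adds: "All reports and communications relating to the study will identify subjects by subject identification and age".

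On blinding, section 3.2 accepts that the trial is open-label but promises that "efforts will be made to keep the assessor blinded to the treatment allocation during the trial to avoid bias in the assessment of subject outcome". Section 6.2 says "All efforts are made to keep the assessor blind" and has any spontaneous disclosure by a child registered. Section 3.4, under the T1 visit, gives a practical measure: "someone else of the trial team other than the assessor should take this satisfaction questionnaire, if possible". It also has the assessor asked whether he or she thinks the child played, to find out whether blinding held. The same paragraph limits the commitment: "As the trial is open, it is not mandatory to keep the assessor blinded". Whether the assessor was in fact blinded is to be recorded.

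**The concern.** A subject code is normally the most widely seen item in a trial: it heads worksheets, eCRF screens and correspondence. If it carries the group, each of these can disclose the arm. The protocol guards against small leaks, such as a child's chance remark or who hands out a satisfaction form, yet section 10.1 puts the same information in the identifier.

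At stake is the credibility of the outcomes that assessor blinding can protect, namely the tasks the child performs at the site visits. They cover planning, social behaviour and working memory. Working memory is also a secondary objective and a proposed mediator (sections 2.3 and 2.4). An assessor who knows the arm could, without intending to, prompt, encourage or score differently.

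**Working it through.** The protocol gives no figure on this point, so the check is a comparison of its sections.

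1. **What the code reveals.** Section 10.1 names two components, group and serial number. Reading the code therefore gives the arm. The restricted list in that section protects the child's identity only; it does not hide the group, because the group sits in the code itself.

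2. **Whether the assessor meets the code.** No section says so directly. Section 10.6 says of the child tasks: "Results on tasks for children (may be added directly in the CRF, but also paper source can be used". Section 10.1 makes worksheets part of the source documentation and requires all study data to be in the CRF. Section 10.5 has subjects identified by their subject identification. No section gives the assessor a separate neutral number or masks the code. Section 6.2 mentions a randomisation number drawn by site and gender, but nothing says that it replaces the section 10.1 code on study records. That the assessor sees the code is therefore a strong inference, not stated text.

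3. **What this does to the blinding measures.** If the assessor sees the code, having a colleague take the satisfaction questionnaire no longer keeps the arm from the assessor. The question whether the child seems to have played would then partly measure whether the assessor read the code. It would still register that blinding failed, but would say little about whether the child or the visit procedures gave the arm away.

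4. **Which outcomes are exposed.**
   - Primary outcomes (section 6.1.3): BRIEF plan/organise, the time management questionnaire and SSIS cooperation, all scored by parents. Section 6.2 says parents will know the allocation. Assessor blinding does not bear on these ratings or on the ANCOVA planned for them in section 8.
   - Teacher ratings: completed online by teachers, who also know the allocation.
   - Child self-efficacy: a self-report by the child.
   - Tower Test and SCVT (section 6.1.2): performed by the child at the visit, with room for assessor influence on administration and, for SCVT answers, possibly on scoring. How the SCVT is scored is not described.
   - Chessboard task: presented on a computer and answered by mouse click, so less exposed.

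5. **Timing.** Section 6.2 places randomisation after baseline data and confirmation of eligibility. In section 3.4, consent and screening precede randomisation, and note f to Table 1 allows the child's T0 tasks to precede it too. A code that contains the group cannot be issued until the group is known. Section 10.1 names no other identifier for the earlier records.

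**The case against.** The strongest reply is that the protocol never makes assessor blinding a requirement. Section 3.4 says it is not mandatory, and its measures are worded as preferences. Section 6.2 calls the trial open-label and expects site staff to know the allocation. This stands: the code works against a best-effort aim and breaks no rule. It does not remove the inconsistency, because section 6.2 treats the assessor separately from other site staff.

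A second reply is that the section 10.1 code may be meant only for anonymised storage, with another identifier in use at visits. That is possible, and the subject identification in section 10.5 is not expressly equated with the section 10.1 code. But no other working identifier is named for the assessor's records.

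A third reply concerns timing. Section 10.1 does not say when the code is issued, and section 10.5 provides a screening log. The timing point is therefore a gap, not a direct contradiction.

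Some stronger readings are tempting but unsupported:

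- A reader might infer that the main result is biased by this. It is not, because the primary ratings come from parents who know the arm in any case.
- A reader might infer that assessors would almost always guess the arm correctly. No rate can be derived, because exposure to the code is itself inferred and children may disclose their condition anyway.
- A reader might take the child tasks to be the only outcomes not rated by a parent or teacher. Child self-efficacy is another.
- A reader might object that data managers and statisticians would see the arm. The protocol nowhere promises that they are blinded.

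**Conclusion.** The point holds in a limited form. As written, section 10.1 puts the allocation into the identifier and so undercuts the effort stated in sections 3.2 and 6.2 to keep the assessor blind; it also weakens the check in section 3.4.

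The code would apply to all 170 planned children, but the consequence is confined to secondary child measures at T1 and T2: chiefly the Tower Test and the SCVT, less so the Chessboard task. The primary analysis and the sample size are unaffected. No size of bias can be calculated from the protocol.

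The conclusion rests on two assumptions: that the section 10.1 code, or an identifier containing it, appears on the materials the assessor uses, and that the assessor understands the coding scheme. Both are likely; neither is stated. The timing gap depends on neither. Severity is minor to moderate.

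**What to change.** Replace the sentence on the subject code in section 10.1 with:

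> Subjects receive an allocation-neutral number (site and sequential number) at consent; the randomised group is not part of the code and is not shown on the worksheets or eCRF screens used by the assessor.

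This also closes the timing gap, since the number exists before screening.

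The allocation should stay available to site staff who need it. Notes d and e to Table 1 give the satisfaction questionnaire to the immediate group at T1 and to the delayed group at T2, so someone at the site must know the arm. Holding the arm only in the randomisation system, or masking all listings until database lock, would go beyond what this design promises and is not needed.

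The cost is one sentence, a numbering setting in the eCRF and a check of what the assessor's screens and worksheets display. No endpoint, visit, sample size or analysis changes.
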